#### **10.2.2. Phase II trials**

Independently for each phase II trial:

- Eligible population: All patients included without major violation of eligibility criteria.
- Eligible population assessable for efficacy: All patients eligible and for whom the following conditions are satisfied:
  - Received at least one complete cycle over the first two cycles (i.e. both Regorafenib and Avelumab received fully over at least one cycle) or two incomplete treatment cycles (i.e. at least Regorafenib or at least Avelumab partially administered over each of the first two cycles),
  - At least one disease measurement recorded not less than eight weeks after treatment onset.
- The following patients will also be included in the population assessable for efficacy; they will be considered as "inevaluable for response" for the primary endpoint as per RECIST v1.1 criteria (i.e. objective response under treatment) and not be replaced in the primary efficacy analysis:
  - Any eligible patients who received at least one treatment cycle or two incomplete treatment cycles and experience disease progression or die due to disease progression prior to response evaluation (will be considered as "inevaluable for response" due to early progression or death related to progression).
- Safety population: all patients who initiated treatment (Regorafenib or Avelumab).

#### Rules of decision for patient's replacement:

- Any patient not eligible or not assessable for efficacy will be replaced.
- However, any patient who received at least one administration of the study drug will be included in the safety analysis.

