##### 10.3.2.2. PHASE II TRIALS

- All analyses will be descriptive; no p-values will be calculated.
- Analyses will be conducted independently for each phase II trial.
- Analysis of the primary efficacy endpoint will be analysed based on the eligible population assessable for efficacy (see chapter 10.2 for definition):
  - Each patient will be assigned one of the following categories:
    - Confirmed complete response (CR)
    - Unconfirmed complete response (CRu)
    - Confirmed Partial response (PR)
    - Unconfirmed Partial response (PRu)
    - Stable disease
    - Progression (Clinical PD and radiological PD will be reported separately)

- Inevaluable for response
- Depending on the cohort, the rate of objective response (ORR: CR, CRu, PR, PRu) under treatment or the progression-free rate (PFR: CR, CRu, PR, PRu, SD) will be reported:
  - All eligible and assessable patients (section 10.2) will be included in the denominator for the calculation of the ORR/PFR.
  - The 95% two-sided confidence limits will be provided for the ORR/PFR (binomial law).
  - First endpoint conclusions will be based on the ORR/PFR for all eligible and assessable patients (section 10.2) after centralized radiological review of the data.
- As regards to the other efficacy endpoints, the analyses will be carried out in the eligible and assessable population:
  - Each patient will be assigned one of the following categories:
    - Confirmed complete response (CR)
    - Unconfirmed complete response (CRu)
    - Confirmed Partial response (PR)
    - Unconfirmed Partial response (PRu)
    - Stable disease
    - Progression
    - Inevaluable for response
  - The rate of best overall response will be calculated as the number of patients alive with the best response (recorded from the start of the treatment) divided by the number of patients eligible and assessable (section 10.2).
  - The 6-month progression-free rate will be calculated as the number of patients remaining alive and progression-free at 6 months from the start of the treatment divided by the number of patients eligible and assessable (section 10.2).
  - The 6-month objective response rate will be calculated as the number of patients alive with complete or partial response at 6 months divided by the number of patients eligible and assessable (section 10.2).
  - The 95% two-sided confidence limits will be provided for the calculated rates (binomial law)
- The safety analysis will be performed on the safety population.

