### DEFINITIONS

Evaluable for toxicity: All patients will be evaluable for toxicity from the time of their first treatment with study drugs.

Evaluable for objective response: Only those patients who have measurable disease present at baseline, have received at least one cycle of therapy, and have had their disease re-evaluated will be considered evaluable for response. These patients will have their response classified according to the definitions stated below. (Note: Patients who exhibit objective disease progression prior to the end of cycle 1 will also be considered evaluable.)

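### Section 10.2.2 removes and replaces some eligible, treated patients because of events after treatment start; almost all are failures, so the phase II primary rates are biased upward

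*Protocol*

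**What the plan says.** Section 10.2.2 sets two conditions for the efficacy population in each phase II cohort. The first is exposure: "Received at least one complete cycle over the first two cycles", or two incomplete cycles. The second is a scan: "At least one disease measurement recorded not less than eight weeks after treatment onset".

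It then adds one group back, to be counted as inevaluable for response and not replaced: patients with at least one cycle or two incomplete cycles who "experience disease progression or die due to disease progression prior to response evaluation".

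Everyone else falls under the replacement rule: "Any patient not eligible or not assessable for efficacy will be replaced". Those who received study drug remain in the safety analysis only.

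Section 10.3.2.2 uses this set as the denominator of the primary rate, and section 10.1.2 does so for the Bayesian cohorts A to G. For the remaining endpoints, section 10.3.2.2 says: "As regards to the other efficacy endpoints, the analyses will be carried out in the eligible and assessable population".

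Appendix 3 (Definitions) has its own rule. Patients must "have received at least one cycle of therapy, and have had their disease re-evaluated will be considered evaluable for response", with this exception: "Patients who exhibit objective disease progression prior to the end of cycle 1 will also be considered evaluable".

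**The concern.** Whether a treated patient counts should not depend on how that patient fared. Here it partly does. A patient who dies of toxicity in week 5, stops for toxicity in cycle 1 and is never scanned again, or progresses before finishing cycle 1 leaves the denominator, and someone else is enrolled instead. Few, if any, such patients could have been a response, a 6-month progression-free case or a disease control.

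Each cohort has a single arm and its rate is compared with a fixed p0, so no control arm suffers the same losses and cancels the effect. Removing failures raises the estimated rate and the chance of declaring an inactive combination promising. It also keeps part of the toxicity cost out of the efficacy result.

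**Working it through.** **Who is kept and who is lost (section 10.2.2)**

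- Progression or progression-death after one cycle or two incomplete cycles: kept as a non-success.
- Progression or progression-death below that exposure: replaced. If the progression is objective and falls before the end of cycle 1, Appendix 3 calls the patient evaluable. This is a direct conflict.
- Death from toxicity or another non-progression cause with no scan at 8 weeks or later: replaced. The add-back covers only deaths due to progression.
- Toxicity stop below the exposure minimum, or with no such scan: replaced. This can include patients who go off study under section 7.6.2 because regorafenib was stopped for good before the first avelumab dose.

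The add-back does not say whether its one cycle must be complete, that is, both drugs fully received. If it must, a patient who progresses after a single interrupted cycle is lost too.

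**The plan's own designs, reproduced**

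Inputs are the decision rules in sections 10.1.3 to 10.1.10. Single-stage cohorts: P(X ≥ r), X ~ Bin(n, p). Two-stage cohorts: sum over x1 > r1 of P(X1 = x1) · P(X2 ≥ r − x1), with X1 ~ Bin(n1, p) and X2 ~ Bin(n − n1, p).

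| Cohorts | Rule | p0 / p1 | Error at p0 | Power at p1 |
|---|---|---|---|---|
| H, A' | stop if ≤3 of 13; success if ≥13 of 43 | 20% / 40% | 0.050 | 0.800 |
| I | stop if ≤2 of 13; success if ≥8 of 29 | 15% / 40% | 0.050 | 0.907 |
| J, L, N | ≥8 of 28 | 15% / 35% | 0.049 | 0.818 |
| K, P | ≥8 of 40 | 10% / 25% | 0.042 | 0.818 |
| M, O | ≥12 of 35 | 20% / 40% | 0.034 | 0.805 |

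The stated error and power hold when every counted patient succeeds with probability p0 or p1.

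**Effect of removing failures (illustration)**

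Assume a share d of treated patients is removed, none of them a success, and the true rate among all treated patients equals p0. The rate in the assessable set is then p0 / (1 − d). For H and A' at d = 10% this is 0.20 / 0.90 = 22.2%. Rerunning each rule at the shifted rate gives the chance of a positive verdict:

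| Cohorts | d = 0 | d = 5% | d = 10% |
|---|---|---|---|
| H, A' | 5.0% | 6.9% | 9.7% |
| I | 5.0% | 6.4% | 8.3% |
| J, L, N | 4.9% | 6.3% | 8.2% |
| K, P | 4.2% | 5.4% | 7.0% |
| M, O | 3.4% | 4.9% | 7.0% |

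The 10% column matches the protocol's allowance of about 10% for non-evaluable patients. A result on the boundary in cohort H is 13/43 = 30.2% of assessable patients but 13/47 = 27.7% of those recruited, if the other four are all failures.

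**Power if those patients are counted instead**

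If p1 was meant for assessable patients, the all-treated rate under the alternative is p1 · (1 − d). At d = 10%, H and A' run at 0.40 × 0.90 = 0.36 and power falls from 0.80 to 0.67. The others become 0.83 (I), 0.70 (J, L, N), 0.71 (K, P) and 0.65 (M, O).

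The same bias applies to cohorts A to G, but its size is not computed here.

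**The case against.** An evaluable-patient set is declared in advance, and the designs were sized on it. The most important early failures, those who progress after modest exposure, are kept. The exposure bar is low, since an incomplete cycle needs only partial administration of either drug. The scan condition has no upper time limit: section 5.6 asks for a tumour assessment at the safety follow-up visit unless progression is confirmed or new treatment has begun, and section 5.7 continues follow-up of non-progressors. Many toxicity stops will therefore have a qualifying scan. All this limits how many patients are lost; it does not make the loss independent of outcome. Nor is it a detail left to the SAP: the protocol fixes both the denominator and the replacement rule.

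Four stronger readings are tempting, but the text does not support them:

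- **That early progressors in general are dropped.** Section 10.2.2 keeps those with one cycle or two incomplete cycles.
- **That Appendix 3 contradicts every exclusion.** It also requires one cycle and re-evaluation. It conflicts only on objective progression before the end of cycle 1, and does not contradict the loss of unscanned toxicity stops or deaths.
- **That every counted patient must survive to a week-8 scan, so that PFS and OS carry full immortal time.** Patients who progress or die of progression enter without one. Only a partial version remains, for non-progression deaths and under-exposed patients.
- **That PFS and OS are explicitly restricted to this set.** Section 10.3.2.2 implies it through the sentence on other efficacy endpoints, but the survival bullet names no population. Any inflation of PFS or OS is expected to be upward but cannot be quantified.

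On size, the objection largely stands. The allowance has no breakdown and may include withdrawals and losses to follow-up. For H and A' it is 4/47 = 8.5%, for which the same calculation gives 8.8%. The documents also do not say whether p0 comes from all-treated or assessable patients.

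**Conclusion.** The point holds in this form. Section 10.2.2 excludes and replaces some eligible, treated patients because of post-treatment events that are almost all failures, so the primary rates are biased upward against a fixed p0. It also conflicts with Appendix 3 on objective progression before the end of cycle 1.

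The size is an illustration, not an estimate. It rests on every removed patient being a failure and on the true all-treated rate equalling p0. Under those assumptions, 5% removed already takes the error above 5% in every design group except M and O. The 10% case is near the upper end of what the planned allowance implies. A reader should not quote 9.7% as the trial's actual type I error.

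**What to change.** - Make the primary denominator all eligible patients who received at least one dose of either drug. Count those without an evaluable assessment as not responding, not progression-free or without disease control, according to the cohort's endpoint.
- Replace only ineligible or never-treated patients.
- Keep the present assessable set as a sensitivity analysis.
- State in section 10.3.2.2 that PFS and OS are analysed in all eligible treated patients.
- Reconcile section 10.2.2 with Appendix 3 on progression before the end of cycle 1.
- Say whether p0 and p1 refer to all treated or to assessable patients, and restate power on the new denominator.

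The edits are textual, but they have a cost. Rates become slightly less favourable. If p1 was meant for assessable patients, power drops as shown in the working (H and A' from 0.80 to about 0.67 with 10% counted as failures). If p1 was meant for all treated patients, the stated power stands, and most of the extra recruitment for non-evaluable patients is no longer needed.

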### 10.3. STATISTICAL ANALYSIS

Two statistical analysis plans (SAP) will be produced by the statistician and validated by the steering committee before (i) the first statistical analysis of the phase I trial and (ii) the first statistical analysis of the phase II trial. At the end of the dose escalation part of the phase I trial and before opening the phase II trials, an IDMC (see section 12) will be set up to assess safety data and validate MTD/RP2D based on the statistical report produced by the statistician of the study.

#### **10.3.1. Patient characteristics at baseline**

For the phase I trial, as well as independently for each phase II trial:

The patients entered into the study will be described according to the following characteristics:

- Compliance with eligibility criteria,
- Epidemiological characteristics,
- Clinical and laboratory characteristics,
- Treatment characteristics.

#### **10.3.2. Endpoint analyses**

##### 10.3.2.1. PHASE I TRIAL (DOSE ESCALATION PART)

- All analyses will be descriptive; no p-values will be calculated.
- Primary endpoint will be analyzed on the population assessable for safety of the phase I trial (escalation part).
- Toxicity observed at each dose level, graded according to the Common Terminology Criteria for Adverse Events v5.0 from the NCI, will be recorded in terms of event type, severity, dates of beginning and end, reversibility and evolution. Data will be gathered in tables summarizing toxicities and side effects for each dose level and cycle.
- DLT will be described in terms of number and incidence rates at each dose level. The number and percentage of patients who will have developed a DLT in each dose level will also be reported.
- Data analyses will be provided by dose groups and for all study patients, combined wherever appropriate.
- Categorical endpoints: best overall response, ORR under treatment and at 6 months, 6-month ORR and 6-month PFR, will be reported in terms of counts by dose level.
- Continuous endpoints, e.g. GMI, will be reported in terms of summary statistics that will include number of patients, median, minimum, and maximum, and additional percentiles if appropriate.
- Survival endpoints (PFS and OS) will be analyzed using the Kaplan-Meier method. The median survival rates will be reported with a 95% confidence interval. Median follow-up will be calculated using the reverse Kaplan-Meier method.
- Missing data will not be imputed.

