| Endpoints               | 
PHASE I TRIAL/ DOSE ESCALATION
 
Primary endpoint
 

• Toxicity graded using the common toxicity criteria from the NC-CTCAE v5

• Incidence rate of DLT at each dose level during the first 28 days.

 
Secondary endpoints
 

• Preliminary signs of antitumor activity in terms of:

○ Best overall response defined as the best response recorded from the start of the study treatment until the end of treatment taking into account any requirement for confirmation as per RECIST v1.1 criteria.

○ Objective response rate (ORR) defined as the proportion of patients with complete response or partial response, as per RECIST 1. ORR under treatment and 6-month ORR will be reported.

○ Progression-free rate (PFR) at 6 months defined as the proportion of patients with complete response, partial response or stable disease more than 24 weeks as per RECIST v1.1 criteria.

○ Progression-free survival (PFS) defined as the time from study treatment initiation to the first occurrence of disease progression or death (of any cause), whichever occurs first. 1-year PFS rate and median PFS will be reported.

○ Overall Survival (OS) defined as the time from study treatment initiation to death (of any cause). 1-year OS rate and median OS will be reported.

○ Growth modulation index (GMI): GMI will be defined for each patient as the ratio of its PFS on Regorafenib + Avelumab treatment to its PFS on the previous line of therapy. This method accounts for inter-patient variability, the patient serving as his/her own control and implies by the

 |                     |                                          |              |  |  |       |      |       |          |              |          |         |    |                                         |         |             |                                        |        |                                          |       |    |   |   |          |         |         |         |             |       |        |        |

natural history of the disease that the PFS tends to become shorter in successive lines of therapy. It is thought that an anti-cancer agent should be considered effective if the GMI is greater than 1.3

- PK measurements expressed as AUC, half-life and concentration peak for Regorafenib

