## 2. OBJECTIVES

### 2.1. PRIMARY OBJECTIVE

#### **2.1.1. Phase I trial**

Primary objective of the phase I trial is to establish the recommended phase II dose (RP2D), the maximum tolerated dose (MTD) evaluated on the first cycle (D1 to D28), the safety profile, and the Dose Limiting Toxicities (DLT) of Regorafenib when prescribed in association with Avelumab (no dose escalation for Avelumab) in patients treated for advanced digestive solid tumors.

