### 8.3. SAFETY

Patients will be evaluable for safety if they have received at least one treatment administration. Safety will be evaluated using clinical examinations, which will comprise vital signs analysis, clinical assessment of AEs, changes in laboratory parameters (hematological and biochemical, including liver function tests) and any other analyses that may be considered necessary. Safety profile will be continuously followed during treatment up to 90 days after the last treatment administration or until the start of a new antitumor therapy, whichever occurs first. All AEs will be classified according to the NCI-CTCAE, version 5.0.

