### **10.2. DEFINITION OF STUDY POPULATIONS**

#### **10.2.1. Phase I (Dose escalation part)**

The following patients will be included in the population assessable for safety (primary analysis):

- Patients who received  $> 75\%$  RDI for Regorafenib AND Avelumab over cycle 1,
- Patients who received  $\leq 75\%$  RDI for Regorafenib OR  $\leq 75\%$  RDI for Avelumab over cycle 1 due to any drug-related AE.

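### The phase I primary toxicity analysis is tied to a DLT-evaluable set defined by cycle 1 dose intensity, although section 8.3 and Appendix 3 make every treated patient evaluable for safety

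*Protocol*

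**What the plan says.** **Objective and endpoint.** Besides the recommended phase II dose (RP2D), section 2.1.1 makes the following part of the phase I primary objective: "the maximum tolerated dose (MTD) evaluated on the first cycle (D1 to D28), the safety profile, and the Dose Limiting Toxicities (DLT"). The Synopsis (Endpoints, phase I, primary) lists "Toxicity graded using the common toxicity criteria from the NC-CTCAE v5" next to the DLT incidence at each dose level, and section 9.1.1 does the same. The primary endpoint is therefore wider than DLTs.

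**Analysis population.** Section 10.3.2.1: "Primary endpoint will be analyzed on the population assessable for safety of the phase I trial (escalation part"). The bullets that follow describe the toxicity tables and the DLT rates and name no other population.

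**Definition of that population.** Section 10.2.1 opens with "The following patients will be included in the population assessable for safety (primary analysis") and admits two groups:
- patients above 75% "RDI for Regorafenib AND Avelumab over cycle 1";
- patients at or below 75% for regorafenib, or at or below 75% "RDI for Avelumab over cycle 1 due to any drug-related AE".

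**Definitions elsewhere.** Section 8.3, which is not limited to one phase: "Patients will be evaluable for safety if they have received at least one treatment administration". Appendix 3 (Definitions): "All patients will be evaluable for toxicity from the time of their first treatment with study drugs".

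**Phase II, for comparison.** Section 10.2.2 defines a safety population of everyone who started either drug. Its replacement rules add that anyone given at least one administration stays in the safety analysis. The phase I part of section 10.2 has a replacement rule but neither of these provisions.

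**The concern.** An RDI-based set is the usual denominator for a DLT rate, because a patient with too little exposure in cycle 1 says little about the tolerability of the dose. It is not the usual denominator for describing toxicity, where anyone exposed can contribute an event. Here one set carries both tasks because graded toxicity and DLTs share the primary endpoint.

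At stake is the completeness of the phase I safety report. Section 10.3 has an independent committee assess the safety data and validate the MTD and RP2D from the statistical report. The Synopsis (Study design, phase 2 trials) bases the RP2D on all the safety data of patients in the escalation part. A report whose primary toxicity analysis omits some treated patients does not match that basis.

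**Working it through.** The plan gives no figure to reproduce on this point, so the check is to find who falls outside the section 10.2.1 set and then to illustrate what that can do to a rate.

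**1. Exposure planned in cycle 1.** Regorafenib is given daily on Days 1 to 21, so 21 dosing days. Avelumab starts on Day 15 of cycle 1 and is given every two weeks (sections 3.2.2 and 7.3), so one dose in cycle 1.

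**2. RDI.** The protocol gives no formula. I assume received divided by planned over cycle 1.
- Avelumab, stopped before Day 15: 0/1 = 0%.
- Regorafenib, 14 days taken: 14/21 = 66.7%.
- Regorafenib, 15 days taken: 15/21 = 71.4%.
- Regorafenib, 16 days taken: 16/21 = 76.2%.

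**3. Who is in and who is out.**
- Stops for progression before Day 15: avelumab RDI 0%, cause not a drug-related adverse event. Outside the set, even after up to 14 days of regorafenib with recorded toxicity. Evaluable for safety under section 8.3 and Appendix 3.
- Stops for progression after 16 or more regorafenib days and the Day 15 avelumab dose: RDI at least 76.2% and 1/1 = 100%. Replaced under the section 10.2.1 replacement rule, yet still inside the set.
- RDI of 75% or less because of a drug-related adverse event: inside the set.
- Goes off treatment for an adverse event judged not drug-related, with RDI of 75% or less: the replacement rule covers a DLT or any other adverse event, so this patient is not replaced and is counted as having had a DLT. The population definition admits low RDI only when the event is drug-related. Read literally, a counted DLT falls outside the set on which the DLT rate is calculated.

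The patients lost to the primary toxicity analysis are therefore those with 75% RDI or less of either drug for reasons other than a drug-related adverse event. They are not the same group as the replaced patients.

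**4. Effect on a rate at one dose level (illustration).** Assume 6 assessable patients and 1 excluded patient.
- Excluded patient had the event: 0/6 (0%) becomes 1/7 (14.3%); 1/6 (16.7%) becomes 2/7 (28.6%).
- Excluded patient did not have the event: 1/6 (16.7%) becomes 1/7 (14.3%).

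**5. Share of treated patients missing (illustration).** The protocol plans 6 to 12 phase I patients and gives no exclusion rate. Assume k = 1 to 3 excluded patients, share = k/(n + k).
- n = 12: 1/13 = 7.7%, 2/14 = 14.3%, 3/15 = 20.0%.
- n = 6: 1/7 = 14.3%, 2/8 = 25.0%, 3/9 = 33.3%.

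**The case against.** The other side has four arguments.

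**Other analyses are not ruled out.** Section 10.2.1 labels its set as being for the primary analysis, and section 10.3.2.1 also promises results by dose group and for all study patients combined where appropriate. Section 8.3 already makes everyone treated evaluable. This stands in part: an additional all-treated summary is possible. But the sentence on combined reporting concerns pooling across dose groups. It defines no all-treated phase I set and does not displace the explicit sentence assigning the primary endpoint to the RDI-based set.

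**This belongs in the statistical analysis plan.** Section 10.3 promises one before the first phase I analysis, and phase I is descriptive throughout. The allocation of individual tables can indeed wait for that plan. The protocol, however, has not left the population open. It states one, and that one conflicts with two other places in the same document.

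**The RP2D is protected.** A reader might infer that the RP2D was chosen on incomplete toxicity data. The documents do not support that. The Synopsis bases it on all safety data from the escalation part, and section 3.2.1 adds safety data from all cycles, PK and PD. The section 7.3 phase II table already records 160 mg as the dose defined in phase I, so what remains affected is phase I reporting, not escalation.

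**Patients who stop for toxicity are kept.** A reader might infer that events of doubtful attribution are systematically lost, or that every replaced patient disappears. Neither follows. The replacement rule does not replace patients who stop for any adverse event, and it counts those with low RDI as DLTs. A patient replaced after more than 75% RDI of both drugs remains in the set. What stands against the plan is that the population definition is narrower than this rule, so the two do not agree.

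**Conclusion.** The protocol contradicts itself on who is evaluable for safety in phase I. Followed as written, its primary toxicity analysis leaves out treated patients whose cycle 1 RDI was 75% or less for reasons other than a drug-related adverse event. The RDI-based set is suitable for DLT rates and the 3+3 decisions; the error is in using it for graded toxicity as well.

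The size cannot be stated from the document. The 7.7% to 20.0% of treated patients missing (14.3% to 33.3% with six assessable) rests on an assumed one to three exclusions. The shift from 0/6 to 1/7 assumes that the excluded patient had the event. A reader might go further and conclude that toxicity is understated. That is possible but not shown, since an excluded patient without the event moves the rate the other way. The RDI calculation assumes received over planned doses.

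**What to change.** - In section 10.2.1, rename the RDI-based set as the DLT-evaluable population and use it only for DLT rates and the 3+3 decisions.
- Add a phase I safety population of all patients with at least one administration of either drug, in line with section 8.3, including patients who are later replaced.
- In section 10.3.2.1, assign the DLT incidence to the first population and all phase I toxicity tables to the second.
- Reconcile the section 10.2.1 population, which requires a drug-related event, with the replacement rule, which covers any adverse event, so that no patient counted as a DLT lies outside the DLT denominator.

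The cost is a wording change and slightly different denominators in the toxicity tables. The data are already collected, and no sample size or design figure changes.
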